# Device Specifications

The NIDEK Gonioscope GS-1 obtains gonioscopic images without using a goniolens or slit lamp. This device captures 360° images of the anterior segment, including the iridocorneal angle, in a single examination. The 16-face multi-mirror prism projects light onto the patient's iridocorneal angle and its peripheral area, and uses an image sensor to generate the image. A coupled gel will be applied to the prism tip prior to using the device. This gel reduces the refraction angle between the patient's cornea and the prism and moderates the variation in each patient's corneal shape.

Although the NIDEK Gonioscope GS-1 is not currently an FDA-approved device, it is a non- significant risk device under the criteria of 21 CFR 812.3 (m):

- - 1. It is NOT intented as an implant and does NOT present a potential for serious risk to the health, safety, or welfare of a subject
    2. It is NOT purported or represented to be for a use in supporting or sustaining human life and does NOT present a potential for serious risk to the health, safety, or welfare of a subject
    3. It is for a use of substantial importance in diagnosing, curing, mitigating, or treating disease, or otherwise preventing impairment of human health and does NOT present a potential for serious risk to the health, safety, or welfare of a subject

# Informed Consent

The study will take place during the course of a single visit. Subjects will be approached by a study team member during a routine clinical visit and will be asked to participate. They will be given ample time to read, understand, and provide informed consent.

Documentation of the informed consent process will be used to ensure that the appropriate questions have been asked to the prospective participant.

# Screening

Eligible subjects will be identified from the clinic through chart review and approached for consent.

# Recruitment, Enrollment and Retention

Subjects will be identified from NYU Department of Ophthalmology and Bellevue Hospital Ophthalmology clinic. Eligibility will be determined based on the results of a patient's eye examination, and qualified subjects will be offered to participate in the study.

# Removal of subjects

Subjects may withdraw their consent for participation in this research study at any time. Any identifiable research or medical information recorded for, or resulting from, subject participation in this research study prior to the date that subject formally withdrew consent may continue to be used and disclosed by the investigators for the purposes described above.

# Primary Analyses

The analysis of the width of the iridocorneal angle will be done according to both the Scheie and Shaffer grading systems. Relationships between results obtained from conventional gonioscopy, ultrasound biomicroscopy, and NIDEK Gonioscope GS-1 will be evaluated by linear and quadratic models, as well as more advanced statistical methods.

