# - Background

Gonioscopy is a vital part of the ophthalmologic examination, as it allows clinicians to evaluate the iridocorneal angle of the eye. The iridocorneal angle contains the orifice to the draining pathway of the aqueous humor from the anterior chamber into the canal of Schlemm. More acute, or “narrow,” angles can put patients at risk for glaucoma due to obstruction of the route of the fluid into the trabecular meshwork. Accumulation of pigment or inflammatory cells can also lead to obstructions of the drainage system and consequent increase in intraocular pressure. Gonioscopy allows clinicians to assess the width of the angle as well as look for any structural deformation or accumulation of material.

The goniolens is a specially designed lens to allow visualization of the angle that is placed on the patient’s cornea by the clinician during the ocular examination. When used in conjunction with a slit lamp, it gives the clinician a view of the iridocorneal angle, which is otherwise masked by the ocular configuration. Although it is considered the gold standard for assessment of the iridocorneal angle, gonioscopy can be difficult to perform. [1] The evaluation of the width of the iridocorneal angle is subjective and requires clinical experience. [1] As such, there is some inter-operator variability in the results obtained using this method.

Due to the time and skill required to obtain an accurate gonioscopic image on a conventional slit lamp, there has been interest in developing alternative methods to obtain quick, accurate, and reliable images of the iridocorneal angle. These alternative methods have involved the use of both new and existing technologies. For instance, currently available 3D Corneal and Anterior Segment Optical Coherence Tomography (3D CAS-OCT) has been used for this purpose. A study investigating the utility of 3D CAS-OCT in evaluating anterior segment parameters found a high degree of intra-grader repeatability, inter-grader repeatability, and correlation with conventional gonioscopy. [2]

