# Primary Outcome Variables

Images obtained by the NIDEK Gonioscope GS-1 will be compared with ultrasound biomicroscopy images and digital gonioscopic images obtained using a goniolens and slit lamp to determine if the NIDEK Gonioscope GS-1 can accurately and reliably capture relevant findings. To determine the accuracy of the NIDEK Gonioscope GS-1, we will use ANOVA to determine if the iridocorneal angle measurements obtained from the NIDEK Gonioscope GS-1 are statistically similar to measurements obtained from ultrasound biomicroscopy and standard gonioscopy. To determine inter-observer reproducibility when using this device, two observers will examine each image obtained from NIDEK Gonioscope GS-1 and separately determine the iridocorneal angle. Inter-observer reproducibility will be determined using Kappa's statistics and intraclass correlation coefficient. Lastly, we will determine if the time it takes to obtain images from the NIDEK Gonioscope GS-1 is statistically different from the time it takes to obtain images by conventional gonioscopy. This will be done via ANOVA.

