# - Methods

# Study Procedure

Subjects who meet eligibility criteria will be identified by study team and will be consented for the study. During their usual ophthalmology visit, all subjects will undergo conventional gonioscopy, ultrasound biomicroscopy, and gonioscopy with NIDEK Gonioscope GS-1. The NIDEK Gonioscope GS-1 will only be used on patients who are in the study. The experimental part of the visit using the NIDEK Gonioscope GS-1 should take approximately 10 minutes,

For conventional gonioscopy, the clinician may obtain digital images of the iridocorneal angle using a slit lamp and goniolens. For ultrasound biomicroscopy, the clinician may obtain ultrasound images that will then be stored within the biomicroscope device. For gonioscopy with NIDEK Gonioscope GS-1, the device may obtain and store images of the iridocorneal angle.

Following collection of the images, one ophthalmologist may examine images obtained from conventional gonioscopy and determine the width of the iridocorneal angle. The same ophthalmologist will determine the width of the iridocorneal angle from the ultrasound biomicroscopy images. This ophthalmologist will be masked to patient names and diagnoses. A second and potentially third ophthalmologists may examine images obtained from NIDEK Gonioscope GS-1 and determine the width of the iridocorneal angle. These ophthalmologists will also be masked to patient names and diagnoses.

Statistical analysis will be performed to determine the association between the findings of iridocorneal angle width in conventional gonioscopy images, ultrasound biomicroscopy images, and NIDEK Gonioscope GS-1 images of each patient. Further statistical analysis will be performed to determine the inter-observer repeatability of the findings of the two ophthalmologists who examined the images from NIDEK Gonioscope GS-1.

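### Angle width is graded, but the named device comparisons treat grades as continuous, so over-reading by GS-1 is attenuated if many eyes sit at the widest grade

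*Protocol*

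**What the plan says.** Primary Analyses (6.7) sets the scale: "The analysis of the width of the iridocorneal angle will be done according to both the Scheie and Shaffer grading systems". Its next sentence says that relationships between conventional gonioscopy, ultrasound biomicroscopy and GS-1 "will be evaluated by linear and quadratic models, as well as more advanced statistical methods".

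Primary Outcome Variables (4.2) gives the accuracy test: "we will use ANOVA to determine if the iridocorneal angle measurements obtained from the NIDEK Gonioscope GS-1 are statistically similar" to those from the two comparators. Agreement statistics appear in the same section, but only between the readers of GS-1 images: "Inter-observer reproducibility will be determined using Kappa's statistics and intraclass correlation coefficient".

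Number of Participants (5.3) sizes the trial on a Cohen's kappa of 0.34 between manual gonioscopy and GS-1. It arrives at 94 eyes, raised to 120 to allow for 10-20% uninterpretable images.

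Study Procedure (6.1) gives the comparator images to one reader: "The same ophthalmologist will determine the width of the iridocorneal angle from the ultrasound biomicroscopy images". GS-1 images go to others: "A second and potentially third ophthalmologists may examine images obtained from NIDEK Gonioscope GS-1 and determine the width of the iridocorneal angle". Background says of conventional gonioscopy: "As such, there is some inter-operator variability in the results obtained using this method".

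**The concern.** A grade is an ordered category on a short scale with two ends. ANOVA and linear or quadratic models compare means as if a reading could always move in either direction by the same amount. An eye already at the widest grade cannot be read wider, so a device that over-reads shows only part of its shift in the mean grade. Eligibility places no limit on angle width, so nothing in the protocol prevents grades from piling up at the wide end.

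A second effect needs one more condition. If GS-1 readings are noisier than the comparator's, error at the top grade can only push readings down, and an unbiased device can look biased. Different readers and different modalities make unequal noise plausible, but the protocol gives no figure for it.

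What is at stake is the primary accuracy result. As written, it would come from methods that do not suit the scale, while agreement between devices, on which the trial was sized, has no named analysis.

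**Working it through.** **Inputs.** From the protocol: graded width, ANOVA and linear or quadratic models (4.2, 6.7), and 94 evaluable eyes (5.3), taken as given. 94/(1 - 0.20) = 117.5, which is consistent with 120 enrolled eyes. The plan gives no figure for a ceiling effect, so there is none to reproduce. Assumed, because the protocol is silent: five grades 0 to 4 with 4 the widest, true width normal with mean mu and SD 1, reading error SD 0.5, and eyes independent. The test is a paired mean test, to which a repeated-measures ANOVA of two modalities reduces.

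**Model.** A reading is true width plus error, rounded and held within 0 to 4. With S = sqrt(1 + error SD squared), the mean grade is

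M(mu, S) = sum over k = 0 to 3 of Phi((mu - k - 0.5)/S).

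For error SD 0.5, S = sqrt(1.25) = 1.118. For error SD 1.0, S = sqrt(2) = 1.414.

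**Step 1, share at the top grade:** Phi((mu - 3.5)/1.118). This gives 9% for mu = 2 (symmetric grades), 33% for 3.0, 50% for 3.5 and 67% for 4.0.

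**Step 2, a true shift with equal noise.** The sums telescope:
- +1 grade shows as Phi((mu + 0.5)/S) - Phi((mu - 3.5)/S).
- -1 grade shows as -[Phi((mu - 0.5)/S) - Phi((mu - 4.5)/S)].

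| Share at top | +1 shows as | -1 shows as |
|---|---|---|
| 9% (symmetric) | 0.987 - 0.090 = +0.90 | -0.90 |
| 33% | 0.999 - 0.327 = +0.67 | -(0.987 - 0.090) = -0.90 |
| 50% | 1.000 - 0.500 = +0.50 | -(0.996 - 0.186) = -0.81 |
| 67% | 1.000 - 0.673 = +0.33 | -(0.999 - 0.327) = -0.67 |

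The loss on the over-reading side is close to the share of eyes at the top.

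**Step 3, no bias but GS-1 noisier.** M(mu, 1.414) - M(mu, 1.118) is 0.00 for symmetric grades and -0.08, -0.11 and -0.12 for 33%, 50% and 67% at the top. For mu = 4.0, for example: (0.993 + 0.961 + 0.856 + 0.638) - (0.999 + 0.987 + 0.910 + 0.673) = 3.45 - 3.57 = -0.12.

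**Step 4, rejection at two-sided 5% with 94 eyes (simulation; repeat runs differ by about one percentage point).**

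| True shift, GS-1 noise | symmetric | 33% | 50% | 67% |
|---|---|---|---|---|
| 0, SD 0.5 | 5% | 5% | 5% | 5% |
| +0.5, SD 0.5 | >99% | >99% | >99% | 97% |
| 0, SD 1.0 | 5% | 12% | 21% | 31% |
| +0.5, SD 1.0 | 97% | 78% | 52% | 25% |
| -0.5, SD 1.0 | about 97% | >99% | >99% | >99% |

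**Step 5, a different model.** Take discrete true grades, equal noise SD 0.7 and 96 eyes (120 x 0.8). A +1 shift shows as +0.41, +0.55, +0.68 and +0.89 with 70%, 50%, 30% and 5% of eyes truly at the top. With no bias and SD 0.7 against 0.4, rejection is 33%, 15% and 7% for 70%, 50% and 30%, and 5% for symmetric grades. A full-grade shift is detected in at least 93% of runs in every setting tried.

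**Step 6, does an ordinal model cure it?** A cumulative-probit mixed model with modality only as a location effect was fitted to unbiased data with noise SD 1.0 against 0.5 (94 eyes, 400 trials per setting). It rejects in 9%, 17% and 28% of trials for 33%, 50% and 67% at the top, little better than the mean test. With a modality-specific scale term, small checks of 100 to 120 trials per setting gave 1% to 8%.

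**The case against.** The strongest reply is that the mean comparison mostly works. With equal noise it holds its 5% level and detects a half-grade over-reading in at least 97% of simulated trials. The larger failures need two things at once, grades piled at one end and a noisier GS-1, and the protocol documents neither. With symmetric grades the false-positive rate stays at 5% even when GS-1 is noisier. All of this stands, and it limits the point.

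Three stronger readings are tempting and are not supported:
- **That the analysis hides over-reading.** It attenuates it. No further shift can be seen in eyes already at the top grade, but a substantial overall shift is usually still detected.
- **That reading noise as such becomes bias.** With equal noise the mean difference is zero under every distribution tried.
- **That over-read narrow angles go unrecorded.** Narrow angles, which Background names as a risk state, have room to move up the scale, so their grade differences are recorded. The ceiling acts on wide eyes, which dilute the overall mean.

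The protocol also leaves unspecified advanced methods open in 6.7, it never calls the grades unbounded, and a statistical analysis plan that is not shown may name an ordinal method. That softens the point but does not remove it: the protocol itself names methods for the device comparison, and none of those named respects the scale.

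**Conclusion.** The point holds in limited form. The between-device methods named in 4.2 and 6.7 suit bounded, ordered grades poorly, and no agreement measure is named for GS-1 against either comparator although the trial was sized on one.

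The size depends on the assumed grade distribution and reading SDs. Over-reading of one grade is reported as about a third to two thirds of a grade when 33% to 67% of eyes are at the top, and as about 0.9 when grades are symmetric. False-positive rates of 12% to 31%, and detection of a half-grade over-reading as low as 25%, arise only if GS-1 is also twice as noisy. These figures treat eyes as independent, although most patients contribute two. The images and readings remain fully usable; the defect is in the named analysis.

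**What to change.** In Primary Outcome Variables (4.2) and Primary Analyses (6.7), make the between-device analysis of graded width an ordinal agreement analysis:
- Show the GS-1 grade by comparator grade cross-table for each comparator, so that over-reading and under-reading are visible at each grade.
- Report weighted kappa with a confidence interval for GS-1 against conventional gonioscopy and against ultrasound biomicroscopy, allowing for two eyes per patient.
- If a shift is modelled, use a cumulative-link mixed model with eye within patient as random effects and a modality-specific scale term. Report the shift with its confidence interval. A location-only ordinal model should not be used, because it carries the same false-positive problem when noise differs.
- Keep ANOVA-type models for acquisition time.

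The cost is wording: the images, readers and sample stay the same. The downside is a somewhat more complex analysis, in which sparse adjacent grades may have to be pooled.

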# - Trial Administration

# Ethical Considerations

This study will be conducted in compliance with the protocol approved by the IRB, GCP guidelines, and applicable NYU Langone Health and federal regulatory requirements. No deviation from the protocol will be implemented without prior review and approval of the IRB,

except where it may be necessary to eliminate an immediate risk to a participant. In such case, the deviation will be reported to the IRB according to its policies and procedures.**7.2 Institutional Review Board (IRB) Review**

This protocol, associated consent form, and any amendments will be submitted to an IRB in agreement with local legal prescriptions, for formal approval of study conduct. The decision of the IRB concerning the conduct of the study will be made in writing to the investigator.

# Subject Costs and Payments

There will be no costs for subjects or payments to subjects when participating in this study.

# Subject Confidentiality

Information about study participants will be kept confidential and managed according to the requirements of the Health Insurance Portability and Accountability Act of 1996 (HIPAA). In accordance with these regulations, participants will sign authorization of the following:

- The protected health information (PHI) that will be collected
- Who will have access to that information and why
- Who will use or disclose that information
- The rights of a research participant to revoke their authorization for use of their PHI

In the event that a participant revokes authorization to collect or use PHI, the investigator retains the ability to use all information collected prior to the revocation of authorization.

Data will be collected after the participant has signed an informed consent form and completed their visit. It will be collected from the medical record, including Epic, and other sources. The collected data include demographics, clinical information and testing results. Data will be collected only by members of the research team and stored in accordance with Federal and University regulations. Research related materials will be retained and stored following NYU policy (a minimum of seven years following study completion). We will use RedCap. ICF's will also be retained for seven years. Paper-based records will be kept in a secure location within a double

locked room and only be accessible to personnel involved in the study. Computer-based files will only be made available to personnel involved in the study through the use of access privileges and passwords, granted prior to access to any study-related information residing within NYU firewall. Data from sub-sites will be periodically transferred to the central site through a secured network connection or by encrypted and password protected hard drives

# Data Collection

Data will be collected only after the participant has signed an informed consent form. The collected data will include demographics, clinical information and goniometry results. Data management will include steps that will ensure confidentiality and security of the data. Data will be collected only by members of the research team and stored in accordance with Federal and University regulations. The data will be de-identified prior and the key will be accessible only by study personnel. Research related materials will be retained and stored following NYU Langone Health policy.

# Data Storage/Security

Research related materials will be retained and stored in a secure MCIT drive following NYU Langone Health policy. Identifiable health information will not be reused or disclosed to any other person or entity, except as required by law or for authorized oversight of the research study.

# Study Monitoring

The Principal Investigator will oversee the safety of the patients. The safety monitoring will include careful assessment and appropriate reporting of adverse events as noted above.

# Data Safety Monitoring Plan

**T y p e s o f D a t a o r E v e n t s**

The following aspects will be specifically monitored: enrollment and retention, data collection, confidentiality, breaches from the study protocol or any adverse event. Adverse events include injury to subjects from the NIDEK Gonioscope GS-1, as described in Section 3.2 of this document.

# R e s p o n s i b i l i t i e s a n d R o l e s f o r G a t h e r i n g , E v a l u a t i n g a n d M o n i t o r i n g t h e D a t a

- - - All study team members will be responsible for reporting data related to unanticipated problems and adverse events
    - If injury occurs to a participant, the ophthalmologist will immediately notify the PI and [name]. A report will then immediately be sent to the IRB from one of these 2 people.
    - [name] will verify data accuracy, by reading it and discussing with co- investigators, once per quarter
    - [name] will verify compliance with the protocol, by comparing actual practice to the protocol, once per quarter.

# I n f o r m a t i o n A b o u t t h e M o n i t o r i n g E n t i t y

- DMC consisting of 3 members:
- [name] (PI), [name] and [name] (Research Coordinator). Contact information can be found elsewhere in the IRB application

# R e p o r t i n g A d v e r s e E v e n t s a n d U n a n t i c i p a t e d P r o b l e m s t o t h e M o n i t o r i n g E n t i t y

- All adverse events will be reported immediately to IRB
- Reporting will be done via email
- [name] or study team members will prepare and submit the form.

# A s s e s s m e n t s

- Monitoring entity will review and assess the data or events captured under the Data Monitoring Plan quarterly. Monitoring entity will review data and events according to assessment criteria for “unanticipated problems involving risks to participants or others” (i.e., as to whether they are unexpected, related and harmful)

# C r i t e r i a f o r A c t i o n

- Any breach of data confidentiality or injury to participants will trigger action
- Study will be stopped if there is injury to a participant

# P r o c e d u r e s f o r C o m m u n i c a t i n g – d i s s e m i n a t i o n o f s a f e t y i n f o r m a t i o n A s A p p r o p r i a t e

- Outcomes of monitoring entity reviews will only be communicated to IRB if an adverse event is found.

The study will be routinely monitored by the PI and the study team during DSMB meetings. The following aspects will be specifically monitored: enrollment and retention, data collection, confidentiality, breaches from the study protocol or any adverse event. The Investigator will also ensure that monitors or other compliance or quality assurance reviewers are given access to all the above noted study-related documents and study related facilities (e.g. diagnostic tests), and have adequate space to conduct the monitoring visit.

Data safety monitoring reviews will occur once per quarter. Adverse events may include loss of data, misplacement of data, or unauthorized access of data. Any and all adverse events will be reported immediately to the IRB by the primary investigator or study personnel by email.

Outcomes of the data safety monitoring reviews will be submitted no less than annually with the continuing review application.

